### Care as Usual (control condition)

Infants randomly assigned to the ‘Usual Care’ group will receive standard follow-up after discharge which does not involve a structured preterm parenting program. Exposure to any structured parenting programs will be reviewed by questionnaire at 6 weeks, 12 months and 24 months C.A. by parental recall.

### Monitoring the intervention

Session checklists will be used to monitor the content delivered. In addition, all Baby Triple P for Preterm infants group sessions and telephone consultations will be video/audio recorded to allow independent protocol adherence checks.

### Concurrent interventions

Both groups may be referred for or receive other concurrent therapies during the period of the study (e.g. physiotherapy, speech therapy, community programs). The content and intensity of any concurrent therapy will be documented by parent recall in questionnaires at 12 and 24 months C.A.

### Clinical ethical considerations

Parents who score >12 on the Edinburgh Post-natal Depression Scale at baseline will be referred to the relevant clinician with the parent’s consent. Parents with elevated scores at 6 weeks post baseline, or 12 months C.A, and/or elevated scores at 24 months C.A. on the Depression Anxiety and Stress Scale will be phoned to discuss referral options. If there are concerns of developmental delay, behavioural problems determined or reported at the determined at 24 month assessment, the managing clinician will be notified. Motor function will be classified by the parent and clinician on the Gross Motor Function Classification System at 24 months C.A [50]. These families will remain in the program and will be included in the full analysis.

## Measures

### Sample descriptors and prediction variables

*Family background questionnaire* (FBQ; assessed at baseline, post intervention, at 12 and 24 months C.A.) Assesses maternal and family factors, socio-economic status, education level and whether it was a planned pregnancy to determine impact on outcome.*Medical risk factors* (assessed at baseline) for outcome from the child’s case notes using the standardised Australian and New Zealand Neonatal network data definitions (e.g. GA, birth weight, disease severity, PIVH [50], PVL) [1].*The Gross Motor Function Classification system* (GMFCS; assessed at 24 months C.A.) is a valid and reliable way to classify the functional abilities of children with cerebral palsy and physical disability.*Social Support Scale* (SSS): will be assessed at baseline, 6 weeks post and 12 months C.A [40]: The SSS is a 4-item measure of the parent’s satisfaction with their social support network. The first two items referred to *formal support* (help that people get from professionals or organisations such as child health nurses or paediatricians) and asked participants to a) list the people they receive formal support from using initials and b) how satisfied they are with the extent of formal support they currently receive (from 1 = *Not at all satisfied* to 5 = *Completely satisfied*). The second two items referred to *informal support* (support that is not paid for and often provided by family, friends and neighbours) and asked participants to a) list the people they receive informal support from using initials and b) how satisfied they are with the extent of informal support they currently receive (from 1 = *Not at all satisfied* to 5 = *Completely satisfied*). Listing people participants receive support from was used as a prompt to think about their support network and these items were not used for data analysis.

### Outcome measures

Assessments will be conducted at baseline, post-intervention (6 weeks) C.A., 12 months (±1 month) C.A. and 24 months (±1 month) C.A. Participants will have the option to complete questionnaires either online or by hardcopy. In the case of hardcopy, questionnaires will be posted to participants (other than at baseline) along with a reply paid envelope for easy return.

### Child outcomes

Primary Outcome Child Behavioural and Emotional Problems:*Infant Toddler Social & Emotional Assessment* [49,51] (ITSEA); will be assessed at 12 and 24 months C.A: This is a primary outcome measure of the study (at 24 months C.A.). The ITSEA is a 165-item parent-report questionnaire to assess social-emotional problems/competencies in the domains of behavioural dysregulation; externalising behaviour; internalising behaviour, and competence Items are presented as statements e.g. “Your child is restless and can’t sit still” and rated on a 3-point scale 0 (not true/rarely) 1 (somewhat true/sometimes) 2 (very true/often). This study will utilise only the externalizing, internalizing and dysregulation subscales. The ITSEA has established concurrent validity, strong test-retest reliability (α = .75-.91) and good internal reliability for each subscale (α = .86 for dysregulation, α = .87 for externalising, α = .85 for internalising, and α = .89 for competence) [49,51].*Observation of mother-child interaction* over 15-minutes will be video-recorded (at 24 months C.A.) during a series of structured tasks to corroborate parent reported data on child behavioural and emotional problems. For example child behaviours coded for are non-compliance, complaint, aversive demands and positive contact. Observations will be conducted in the hospital and will consist of four timed segments: 3 minutes of free play with toys provided, 5 minutes of a compliance task where the parent instructs the child to work with them on a paper and crayon task involving the parent giving simple instructions to the child; 5 minutes where the parent is made ‘busy’ by completing a questionnaire, and 2 minutes of a second compliance task in which the parent instructs the child to pack up the toys. Steps will be taken to reduce the effects of reactivity by positioning the camera as far away as is reasonable and having the researcher leave the room between segments. Coding of the observations will be done by a researcher and trained research assistants using the Family Observation Schedule (FOS [52];which has demonstrated reliability and discriminant validity [15,48,53,54]. The FOS is a microanalytic coding system in which the presence or absence of particular behaviours of both the child are scored in consecutive 10-s intervals. Where the child has a physical disability the tasks will be modified.*Observation of mother-child interaction (6 weeks and 12 months CA).* Participants living within 100 kilometres ‘*as the crow flies’* from Brisbane, will complete a video-recorded mother-infant observation conducted in the mother’s home at 6 weeks and 12 months CA. At 6 weeks CA the researcher will instruct the mother to position herself face-to-face with the infant. The mother will then be instructed to interact the way she normally would with her infant, and to attend to any care the infant may require, for example, feeding. The observation will be recorded for 15-minutes. At 12 months CA the researcher will again instruct the mother to interact the way she normally would with her child, this time through a series of 5 segments: 2-minute interaction with a pop-up toy; a limited physical availability task involving a 3-minute telephone call from the researcher to the mother; 4-minute interaction with a set of blocks; 4-minute interaction with a puzzle; 6-minute interaction with a train set. The mother will be instructed to pack up each toy between segments. The observation will be recorded for 20-minutes. Both observations will be coded using the Emotional Availability Scales (EA Scales) [55] by two independent coders blind to group allocation. The measure assesses the quality of the mother-infant relationship across four caregiver scales (sensitivity, structuring, nonintrusiveness and nonhostility) and two child scales (responsiveness and involvement). The scale has high inter-rater reliability: sensitivity (.89), structuring (.91), nonintrusiveness (.86), nonhostility (.76), responsiveness (.88) and involvement (.87) [56].*Baby Behaviour Inventory* (BBI): will be assessed at 6 weeks post and 12 months C.A. The BBI is a 14-item measure of problematic baby behaviour with three scales: an intensity scale, a problem scale and a confidence scale. Each item describes an infant behaviour e.g. “Baby waking more than four times per night”. For the intensity scale parents indicate how often this behaviour occurs with their baby on a 5 point scale 1 (Never) 2 (Seldom) 3 (Sometimes) 4 (Often) 5 (Always). Parents then indicate if they experience the behaviour as a problem (yes/no) (problem scale) and if so then they rate their level of confidence in dealing with the problem on a 5 point scale 1 (Never confident) 2 (Sometimes confident) 3 (Confident) 4 (Very confident) 5 (Extremely confident). The BBI has reasonable internal consistency (α = .84 for overall intensity scale) and test-retest reliability (*r* = .70, .59 and .57 for the intensity, problem and confidence subscales respectively) and demonstrated construct validity [40].

*Child Cognition and Language:*
*The BSID III* [57] will be administered at 24 months C.A. to assess early cognitive development, language and motor abilities. It takes up to 1.5 hours to administer.*The CSBS DP Infant-Toddler Checklist* [58] will be completed by mothers during the ‘parent busy’ segment of the mother-toddler observation conducted at 24 months CA. For use with parents of children from 6 to 24 months of age, the ITC is a broader developmental screen that identifies children with developmental, in particular language and communication delays as well as children with an autism spectrum disorder (ASD). The ITC consists of 24 questions about early social communication behaviour (e.g. "Does your child let you know when he/she needs help or wants an object out of reach?"). Each item is rated on either a 3 or 4-point scale i.e. Not Yet (0), Sometimes [1], Often [2]. Sensitivity of the ITC for identifying developmental delays is 83%.*Maternal Infant Responsiveness Instrument* [59] (MIRI); will be assessed at 6 weeks and 12 months CA. The MIRI is a 22-item self-report questionnaire measuring maternal responsiveness to infant cues with high internal consistency (α = 0.87) [60] and face and content validity that has been established using advanced nurse practitioners and maternal child nursing experts [59].*Maternal Postnatal Attachment Scale*: (MPAS) will be assessed at 6 weeks and 12 months CA [61]. The MPAS is a 19-item self-report questionnaire measuring mother-to-infant attachment. It has high internal consistency (α = 0.78, 0.79 and 0.78) at four weeks, 4 months, and 8 months respectively, and construct validity that has been established with significant negative correlations with infant temperament and maternal negative affective states [61].*Parenting Scale* [62] (*PS)*: assessed at 24 months CA: The PS is a 30-item measure of 3 dysfunctional parenting styles: laxness (α = .83); over-reactivity (α = .82) and verbosity (α = .63). Reliability is strong (α = .84). Each item requires the parent to rate the likelihood of using a particular discipline strategy in response to common child misbehaviours using a 7-point Likert-type scale. Item scores are summed then averaged to give a total score ranging from 1 to 7. The PS is a valid and reliable tool, with good test–retest reliability (r = .84) and strong discriminant validity between parents of clinic/non-clinic children. The PS has been recommended as a tool for measuring parenting skill [62,63].*Parenting Scale* (PS-12 M): has been adapted for parents of children aged 12 to 18 months and will be assessed at 12 months CA [64]. A 21-item measure that has been adapted to match the language, behaviour and parent–child interactions appropriate for younger children 12–18 months of age. Each item requires the parent to rate the likelihood of using a particular discipline strategy in response to common challenging behaviours using a 7-point Likert-type scale. Item scores are summed to give a total score. Factor analysis revealed a one factor solution with good test reliability (r = .56, p = .01) and strong convergent validity (r = −.77, p = .006).*Maternal Self-Efficacy Scale* (MSES) [44]: will be assessed at 6 weeks post intervention, then at 12 and 24 months CA. The MSES is a 10-item measure of parents’ self-efficacy that has good internal consistency (α = 0.86) and a strong concurrent validity with the PSI Sense of Competency Scale [65]. At 24 months, an adaptation of this scale for toddlers will be used [44].*Brief Child Abuse Potential Inventory* [66] (BCAP): will be assessed at 24 months CA. The BCAP is a 33-item measure of the potential for child abuse with strong internal consistency (α = 0.89) and correlation (*r* =0.96).*Edinburgh Postnatal Depression Scale* [67] (EPDS): will be assessed at baseline, at 6 weeks post intervention then at 12 months CA. The EPDS is a 10-item screen for postpartum depression with good internal (α = 0.80) and test-retest (α = 0.77) reliability.*Depression, Anxiety and Stress Scale-21* [68] will be assessed at 24 months C.A. The DASS-21 is a 21 self-report item questionnaire reflecting the frequency or severity of the participant’s experiences with depression, anxiety and stress over the past week with high internal consistency (α = 0.83, 0.78 and 0.87 for depression, anxiety and stress respectively [69]. High convergent validity has been established between the DASS and other measures of similar constructs: DASS depression scale and the Beck Depression Inventory *(r* = .76), DASS anxiety scale and the Beck Anxiety Scale (*r =* .74*)* and DASS stress scale and the Positive and Negative Affect Schedule (*r* = .74) [70].*Relationship Quality Index (RQI* [69]; will be assessed at baseline, at 6 weeks post intervention then at 12 and 24 months CA [69]. The RQI is a 6-item questionnaire of relationship satisfaction with good internal consistency (α = .68-.86), reliability (α = .90) and discriminant validity. The scale consists of 5 specific items regarding relationship health and 1 global item reflecting global overall relationship satisfaction. A higher score corresponds to higher relationship satisfaction. The RQI has good internal consistency (α = .68-.86;) [69] and reliability (α = .90).*Frequency and Acceptability of Partner Behaviour* (FAPBI) [71]: will be assessed at baseline, at 6 weeks post intervention, then at 12 months CA. The FAPBI is a 19-item measure of the frequency and acceptability of positive and negative partner behaviours with strong internal consistency (α = .73-.85), correlation (*r* = .43-.58) with partner-reports and strong discriminant validity between couples seeking marital therapy and non-clinic couples.*Rapid KPI coding system* [72]: will be assessed at baseline, then at 6 weeks post treatment and 12 months C.A. The KPI will be used to code a video or audio recorded 10-min observation of couple interaction for parents in a relationship, discussing a topic of current conflict. Parents will be provided with a list of possible topics centring on baby care tasks or couple issues. Parents living within a 100 km radius of Brisbane will complete the task either in-home or at the hospital, video-recorded by a researcher. Couples who live beyond 100kms will receive an audio-recorder to complete the task independently, and will post this back using a reply paid envelope. Couple communication is scored in 30s intervals for conflict, validation and verbal affect. The KPI has good internal consistency (positive discussion: κ = .65, validation: κ = .58, invalidation κ = .69, conflict κ = .62, and negative nonverbal behaviour κ = .59 [72], is sensitive to change and has been used to measure changes in couple communication from couple’s therapy [72-74].*Parent Problem Checklist – Baby* (PPC-B): will be assessed at 6 weeks post intervention then at 12 months CA [75]. The PPC-B is a 16-item questionnaire which measures conflict between parents over child rearing. The PPC-Baby has demonstrated strong internal consistency (α = .70) and good test-retest reliability (*r* = .90) with a subset of clinic parents who completed the scale again after an 8-week interval [75].*Parenting and Family Adjustment Scale* [76]. (PAFAS): will be assessed at 24 months C.A. The PAFAS assesses parenting practices and parent and family adjustment. It consists of a 28-item Parenting Scale encompassing two domains including parenting practices (17 items) and parent–child relationship (11 items) and of a 12-item Family Adjustment scale encompassing three domains including parental emotional maladjustment (5 items), family relationships (4 items) and parental teamwork (3 items). Each item is rated on a 4-point scale from not true of me at all (0) to true of me very much [3]. This study will use only the three items from the parental teamwork domain which has good internal consistency (coefficient H = .85). The PAFAS has satisfactory construct and predictive validity [76].*Client Satisfaction Questionnaire* (CSQ): will be administered at 12 and 24 months C.A. for the intervention group only. The CSQ is a 10 item measure of the parent’s satisfaction with the parent training program. It is an adaptation of the Therapy Attitude Inventory (TAI) [77]. The TAI has established reliability, internal consistence and discriminant validity.

### Analyses

Analysis will follow standard principles for randomised controlled trials using 2-group comparisons performed using all subjects for whom outcome data are available, on an intention-to-treat basis. The experimental unit is a family. The effect of clustering for children in multiple births will be partitioned from the experimental error, which will be estimated from the between family variability. Up to 50% of eligible families may not consent or alternatively, be back-transferred to regional hospitals before an approach can be made, and a further 15% may be lost to follow-up at 2 years. Consequential threats to external and internal validity will be checked using baseline and descriptive information for eligible families. Imputation techniques will be used to avoid bias which may be a consequence of non-ignorable missing data during follow-up. All data analyses were performed using STATA 10.0 (Statacorp 2007).

The primary endpoint at 24 months C.A. is the child behavioural and emotional problems as measured on the ITSEA and the mother-toddler observation. This comparison will be between treatment groups using general linear models, with terms included for stratification and important confounding variables, such as the extent of brain injury and socio-demographic variables. Secondary analyses will use similar methods to compare the outcomes between groups for the additional outcomes (cognition, language etc.). For dichotomous outcomes, comparison will be by chi-square tests and multiple logistic regression. Where continuous data exhibit substantial skewness not overcome by transformation, non-parametric methods (Mann–Whitney *U* test) will be used for simple comparisons. Further analysis will be performed using latent growth modelling (LGM) [78,79] as it provides simultaneous analysis of time points and can incorporate latent measures corrected for measurement error [80]. The added-growth LGM used in evaluating the efficacy of Baby Triple P for Preterm infants tests the extent to which the intervention alters the trajectory of the target behaviour [79]. The models may incorporate main effects of time-independent and dependent covariates (e.g. control variables) on trajectories, as well as interactions of such measures with intervention effects [78,79]. The models express the expected change in dependent variables as a function of exposure to the intervention (e.g. Baby Triple P for preterm infants versus Control).

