### Sample size

The sample size needs to be sufficient to provide reliable evidence about whether family functioning is sufficiently impacted by the Baby Triple P for Preterm infants intervention to improve the primary outcome of child behavioural and emotional problems. A clinically important difference in child behavioural and emotional problems is considered to be a standardised effect size of 0.33 on the ITSEA [49]. This is a conservative estimate of the expected effect size observed in past RCTs of Triple P [36]. With a type-1 (alpha) level of 0.05, and 80% power, a total of 140 per group are required for analysis. Based on our experience, the expected retention rate is > 85% so that 330 families (n = 165 in each group) will be recruited to allow for attrition. As babies of multiple births cannot be considered independent, the unit of randomisation is family (or delivery), and the total number of babies recruited will depend on the number of multiple births. A total of ~675 families of preterm infants born at <32 weeks who survive to term equivalent are admitted to RBWH and MMH combined over the proposed 3 year recruitment period. Allowing for the estimated retention rate of 50% of those eligible, the feasibility is high of recruitment of a sufficient sample of at least 330 of the eligible 338 families to be studied at 24 months C.A.

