Overall, 4 modules will be delivered as 2 hour group sessions in each hospital by psychology graduates and/or clinical nurses who have completed Triple P facilitator training. A parent workbook accompanies the program and is given to parents for use with exercises and as a reference. Parents complete homework tasks between sessions to consolidate learning. A flexible approach to delivery format is essential. If group sessions are not possible then individual sessions will be provided. Any family discharged from hospital prior to session completion will be provided with a DVD of missed modules to be watched at home followed by a telephone consultation with their facilitator. After hospital discharge and completion of the first four modules, 4×30-min telephone consultations are conducted with the family in their community by the trained Triple P facilitator who conducted the hospital-based sessions. The telephone sessions provide additional support to parents as they put into practice what has been learnt and the facilitator will assist parents in setting and reviewing parenting goals. Upon completion of all 8 sessions participants will be provided with contact details of their nearest community-based Triple P support location and encouraged over a 2 year period to access these services including seminars, groups and enhanced individual support if required. In addition we will provide intervention participants with ongoing intervention maintenance in the form of Triple P tip-sheets every 3 months (providing developmentally appropriate advice on parenting infants) with ongoing phone support if required, and brief fortnightly text messages reiterating program content.

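### The error term and sample size allow for siblings but not for parent groups or facilitators in the intervention arm; if outcomes correlate within these, the interval is too narrow and power is below that stated

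*Protocol article*

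**What the plan says.** **Analyses.** The family is the experimental unit. Clustering of children from multiple births will be "partitioned from the experimental error, which will be estimated from the between family variability". The primary comparison is a general linear model with stratification and confounder terms. No term for parent group or facilitator is named.

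**Study treatments.** "Overall, 4 modules will be delivered as 2 hour group sessions in each hospital by psychology graduates and/or clinical nurses". After discharge, the facilitator who ran those sessions also holds four 30-minute telephone consultations with each family. Individual sessions replace groups where groups are not possible. Families discharged early receive a DVD of the modules they missed, followed by a call.

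**Care as Usual.** This arm has no structured preterm parenting programme, so it has no treatment groups.

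**Sample size.** The target is "a standardised effect size of 0.33 on the ITSEA" at alpha 0.05 and 80% power: "a total of 140 per group are required for analysis". Then "the expected retention rate is > 85% so that 330 families (n = 165 in each group) will be recruited to allow for attrition". The only dependence recognised is between babies of the same delivery, and it is handled by randomising families.

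**The concern.** Families taught together share a facilitator, discussion and peer support, and the programme content itself includes coping and social support. Their children's outcomes may therefore be correlated. Control families have no such link, so the design is partially nested, with clusters in one arm only.

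An error term taken from between-family variability treats families in the same group as independent. With a positive correlation, the variance of the intervention-arm mean is larger than the model assumes. The confidence interval for the 24-month ITSEA difference would then cover less often than 95%, and the sample would carry less information than the power statement claims. A borderline positive result could look firmer than it is.

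**Working it through.** **Inputs from the Sample size section.** d = 0.33, alpha 0.05 (two-sided assumed), 80% power, 140 analysed per arm, 85% retention.

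**Inputs assumed.** Families per group (m) and within-group ICC. Neither is in the article.

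**Step 1: reproduce the plan's figure.** n = 2 × (1.96 + 0.84)² / d².
- d = 0.33 gives 144.1, so 145 per arm. d = 1/3 gives 141.3, so 142.
- One-sided alpha gives 114 or 112 and does not fit.
- 140 / 0.85 = 164.7, so 165, which matches exactly.

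The stated 140 therefore corresponds, to within rounding, to independent families with no design effect.

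**Step 2: power without clustering.** SE = √(2/140) = 0.1195, and power = Φ(0.33/0.1195 − 1.96) = 78.8% (79.6% with d = 1/3). This is the baseline for what follows. The gap from 80% has nothing to do with clustering.

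**Step 3: add clustering in the intervention arm only.**
- DE = 1 + (m − 1) × ICC
- SE = √((1 + DE)/140)
- Power of a test that uses this SE = Φ(0.33/SE − 1.96)
- True type I error of the planned test = 2 × (1 − Φ(1.96 × √(2/(1 + DE))))

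Example, m = 6 and ICC 0.05: DE = 1.25 and SE = √(2.25/140) = 0.1268. Power = Φ(2.603 − 1.960) = 74.0%. Type I error = 2 × (1 − Φ(1.848)) = 6.5%.

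| m | ICC | DE | SE ratio | Power | Type I error | CI coverage |
|---|---|---|---|---|---|---|
| – | 0 | 1.00 | 1.000 | 78.8% | 5.0% | 95.0% |
| 4 | 0.01 | 1.03 | 1.007 | 78.2% | 5.2% | 94.8% |
| 2 | 0.05 | 1.05 | 1.012 | 77.8% | 5.3% | 94.7% |
| 3 | 0.05 | 1.10 | 1.025 | 76.9% | 5.6% | 94.4% |
| 6 | 0.05 | 1.25 | 1.061 | 74.0% | 6.5% | 93.5% |
| 8 | 0.05 | 1.35 | 1.084 | 72.1% | 7.1% | 92.9% |

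**Step 4: which group sizes are plausible.** With 165 intervention families, two hospitals and 36 months, 165 / (2 × 36) = 2.3 families per hospital per month, if recruitment is even and equally split. A closed group of 6 would take about 6 / 2.3 = 2.6 months to fill, and a group of 8 about 3.5 months. Groups of 2 or 3 are therefore at least as plausible as larger ones.

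**Step 5: could enrolment absorb the loss?** At m = 6 and ICC 0.05, the planned precision needs 140 × 2.25/2 = 157.5, so 158 analysed per arm. Then 158 / 0.85 = 185.9, so 186 per arm or 372 in total. The article expects only 338 families to be available, against a target of 330.

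**The case against.** **The analysis plan is not shown.** That would answer a missing detail. Here the article addresses clustering, names one source and fixes the error term. A later plan that added a group effect would depart from it.

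**The correlation may be negligible.** The endpoint is child behaviour at 24 months corrected age, long after four neonatal-period sessions, and the calls are tailored to each family. No ICC is cited, so 0.05 is only an illustration. This stands, and the point must stay conditional on a positive ICC.

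**Delivery is flexible and groups may be small.** This also stands. Individual or DVD delivery dilutes the group effect, although families with the same facilitator remain linked.

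**Covariate adjustment could recover the power.** In the m = 6, ICC 0.05 case the variance rises by a factor of 2.25/2 = 1.125. Covariates explaining 1 − 1/1.125 = 11% of the outcome variance would offset that. This helps power only. It does not correct an error term that ignores the clusters.

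**Type I error need not be inflated.** Families are individually randomised. If neither the programme nor its group setting affects any family, treatment creates no group component and the test keeps its level. Inflation needs group or facilitator effects that average to zero, or correlation arising from group membership itself. The type I figures above carry that condition.

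**Conclusion.** The point holds in conditional form. The delivery described under Study treatments creates possible clusters in one arm, and neither the fixed error term nor the sample size allows for them. For any positive within-group or within-facilitator correlation, the standard error is understated. On the assumed values the effect runs from trivial (0.6 points of power at ICC 0.01 with groups of 4) to moderate (78.8% down to about 72%, with coverage near 93%, at ICC 0.05 with groups of 8). These figures take every intervention family to be in a group.

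Three stronger readings are not supported:
- A reader might infer that the interval is certainly too narrow. The article gives no ICC, so only the direction under a positive ICC is established.
- A reader might take an extreme case as the expected one. Groups of 8 with an ICC of 0.10 would give 66% power and 9.2% type I error, but nothing in the article supports that ICC, and the recruitment pace makes such groups slow to fill.
- A reader might fault the model for not naming hospital. The covariate list under Analyses is open-ended, and stratifying by hospital is a design preference, so this is not an error in the plan.

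**What to change.** 1. Record the parent group and the facilitator for each intervention family.
2. Replace the error-term sentence under Analyses with a partially nested mixed model. It should have a random parent-group effect in the intervention arm only, individually treated and Care as Usual families as clusters of one, and the family effect kept for siblings.
3. Add a sensitivity analysis that clusters by facilitator, because the group effect alone does not capture links between families who share a facilitator across groups or in individual sessions.
4. Restate power under Sample size with a declared group size and ICC, without enrolling more families.

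The cost is two data fields and revised wording in two sections. The interval will be slightly wider and the stated power lower. If groups are small, the group variance may be imprecisely estimated. If the ICC is near zero, little is lost.
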